### Analyses

Statistical analysis is conducted using SPSS (IBM Corp). The Kolmogorov-Smirnov test will be performed to assess the normality of the data distribution. Type III sum of squares is set to evaluate the hypotheses.

A mixed-design ANOVA will be used to determine whether supplementation affects the blood biochemistry parameters (inflammation and oxidative stress) and physical health (body composition, skin, cognitive function, and vascular health) at baseline, 3 months, and 6 months among the groups. The Mauchly test of sphericity will be conducted to assess homogeneity of variance and compare the means of the supplemented group with those of the placebo group. To account for the risk of a Type I error as a result of many primary and secondary outcomes, multiplicity correction procedures will be used. In particular, the Benjamini-Hochberg approach for false discovery rate control will be used in each outcome domain (eg, oxidative stress markers, inflammatory markers, cognitive tests). Statistical power and Type I error control are balanced for exploratory research in this method with connected variables. The Tukey post hoc test will be used for comparisons between groups, while the Dunnett test will be used for comparisons within groups over time. In terms of missing data, linear mixed-effects models with the missing at random assumption will be used, which is acceptable given the repeated-measures design and inclusion of observed predictors. Nevertheless, dropout rates in older adult groups might differ from missing at random (for example, because of undetected health decline). To evaluate the possible impact of data missing not at random, sensitivity analyses will be conducted using pattern-mixture models and multiple imputation with delta-adjustment scenarios. These methods aid with determining the robustness of the findings under alternate missingness assumptions. All data will be presented as mean (SD), with statistical significance defined as *P*<.05.

This study requires a total of 220 volunteers as calculated using the power and sample size program. In the case where any participant withdraws or is eliminated during the course of the project, their ID number is not reused. Instead, new volunteers are recruited to maintain the total sample size at 220. The distribution of the IP numbers is rerandomized and adjusted as needed to ensure that both groups remain equally balanced, with 110 participants receiving each IP.

All randomized participants are included in the primary analysis using the intention-to-treat approach, which analyzes participants based on their initial group allocation regardless of whether they adhere to the intervention. Only participants who complete the study without significant protocol deviations are included in a secondary per-protocol analysis.

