### Sample Size

Sample size estimation was based on a comparison of mean low-density lipoprotein levels, referencing a previous case-control study on biomarkers for premature coronary artery disease by Shukor et al [99]. The sample size was calculated using a power and sample size program. The effect size was calculated based on a mean value of 3.11 (SD 0.81) for group one and a mean value of 2.66 (SD 1.25) for group two.

The total number of required participants calculated per group of the experimental design was 93 when dichotomous outcomes were presumed with a Type I error probability, α of .05, and power of 0.8. To maintain the power, a 20% dropout rate was factored in. Consequently, 110 participants are required to be enrolled in each group (placebo and supplementation). Therefore, a total of 220 participants are required to perform this clinical study.

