### Recruitment

The selection of potential trial participants is conducted by the PI based on the inclusion and exclusion criteria. Participants who fail to meet the inclusion and exclusion criteria are defined as screening failures. The PI maintains a Screening Log, which includes screen failures to ensure a systematic selection of participants. Informed consent is obtained from each participant by the contract research assistants. During enrollment, general information (name, gender, age, address, and contact information) is obtained. To ensure security and confidentiality, each participant is assigned a participant-specific code. The code is used to label the participant’s laboratory results. Each participant is reimbursed for standard transportation fees.

Participants are free to withdraw from the study at any time for any reason. Participants may also be withdrawn at any time at the discretion of the PI. Possible reasons for withdrawal include abnormal laboratory values, protocol violation, the participant requiring the use of an unacceptable concomitant medication, participant not complying with protocol procedures, participant developing a condition during the study that violates the inclusion or exclusion criteria, loss to follow-up, death, or any other reason in the PI’s opinion that would impede participation in the study.

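### Late allocation is adjusted to refill 110 per product after withdrawals, so it follows earlier losses by arm, and the 220 total does not match the intention-to-treat set

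*Protocol article*

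**What the plan says.** All of this is in the Protocol article.

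- **Sample Size.** The requirement is 93 per group. Then "a 20% dropout rate was factored in", giving 110 per group and 220 in total.
- **Assignment of Interventions.** Numbers 1 to 60 are put in random order for each block of 60 participants. Even numbers get one product and odd numbers the other, so a full block is balanced. This repeats until 220 are recruited. Nothing in that section reacts to withdrawals.
- **Interventions.** Contract research assistants generate the sequence, enrol participants and assign them. Each group's supply carries its own product number, so there are two codes.
- **Analyses.** A withdrawn participant's ID is not reused, and "new volunteers are recruited to maintain the total sample size at 220". Next: "The distribution of the IP numbers is rerandomized and adjusted as needed to ensure that both groups remain equally balanced", with 110 receiving each product.
- **Analyses, closing paragraph.** "All randomized participants are included in the primary analysis using the intention-to-treat approach", by initial allocation and regardless of adherence.

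**The concern.** Two statements in the Analyses section meet badly with the rest of the article.

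First, restoring 110 per product after losses can only be done by sending new people to the arm that lost more. The next assignment then comes from a running tally of losses and not from the block list. Anyone who both enrols participants and knows the tally by product code can foresee it. Replacements also arrive late, so an arm that loses more ends up with more late recruits.

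Second, a total held at 220 with 110 per product counts only people who have not left. The primary analysis set is everyone randomized. Both cannot describe the same group once one person has been replaced, and the article does not say how leavers and their replacements are counted.

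At stake are the concealment of the late assignments and an unambiguous primary analysis set, both of which can still be settled before the product codes are revealed.

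**Working it through.** **1. The plan's own figure.** Inputs from Sample Size: "a mean value of 3.11 (SD 0.81) for group one and a mean value of 2.66 (SD 1.25) for group two", "with a Type I error probability, α of .05, and power of 0.8". A two-sided test is assumed, since sidedness is not stated.

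- Difference = 3.11 − 2.66 = 0.45. Root-mean-square SD = √((0.81² + 1.25²)/2) = 1.053.
- n per group = 2 × 1.053² × (1.960 + 0.842)² / 0.45² = 86. With 20% loss, 86/0.80 = 107.5, so 108, within two of the stated 110.
- The stated 93 is not reproduced by this formula. Starting from 93, 93 × 1.2 = 111.6 (112) and 93/0.80 = 116.25 (117), and 110 allows a loss of 1 − 93/110 = 15.5%.

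**2. Is replacement needed for power?** Power = Φ(0.45 / (1.053 × √(1/n₁ + 1/n₂)) − 1.960).

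| Analyzed per arm | Power |
|---|---|
| 88 and 88 (110 less 20%) | 0.809 |
| 92 and 84 | 0.808 |
| 110 and 110 (fully refilled) | 0.887 |

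On the article's own means and SDs, 220 randomized without replacement already covers a 20% loss, and unequal arms cost about 0.001.

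**3. How many are randomized if 220 is maintained?** The loss rates are assumptions, apart from the planned 20%. If replacements drop out at the same rate, the total is 220/(1 − loss).

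| Loss | Randomized |
|---|---|
| 5% | 232 |
| 10% | 244 |
| 15% | 259 |
| 20% | 275 |

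Counting only the first round at 20%, it is 220 + 44 = 264. Either way it exceeds 220.

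**4. Where do the replacements go?** First round, 110 per arm, assumed losses:

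| Loss, arm A / arm B | People lost | Share of replacements sent to A |
|---|---|---|
| 20% / 20% | 22 / 22 | 50% |
| 25% / 15% | 27.5 / 16.5 | 27.5/44 = 62.5% |
| 30% / 10% | 33 / 11 | 33/44 = 75% |

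**5. Calendar time.** Take the 25%/15% case with everyone randomized kept. Replacements make up 27.5/137.5 = 20.0% of arm A and 16.5/126.5 = 13.0% of arm B. If replacement recruits differ from the first recruits by an assumed 0.3 SD on an outcome, the arms differ by 0.070 × 0.3 = 0.02 SD with no treatment effect. If only the refilled 220 were analyzed, it would be (0.25 − 0.15) × 0.3 = 0.03 SD.

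**6. Would the unaltered list give 110/110?** Not necessarily, even with no withdrawals: 220 = 3 × 60 + 40, so it stops inside the fourth block. Exact equality is not something the block scheme promises.

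**The case against.** The strongest reply is that the article already fixes the analysis set. The closing paragraph of Analyses keeps all randomized participants in their initial group, IDs are not reused, and mixed models, pattern-mixture models and delta-adjusted imputation are planned for dropout, which presupposes that leavers are analyzed. On that reading 220 is only a recruitment target. This largely stands. What it leaves is a count that is not reconciled with the set.

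A reader might infer more, and the article does not support it:

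- **That intention-to-treat is broken.** Recruiting extra people does not remove anyone from the analysis. Exclusion of leavers is nowhere stated.
- **That replacement selects on outcome.** The Recruitment section does say "Possible reasons for withdrawal include abnormal laboratory values, protocol violation", and laboratory tests are primary endpoints. But such withdrawals leave the same missing data whether or not someone new is recruited, and a new volunteer's prognosis does not depend on who left.
- **That counting dropout twice harms validity.** It only adds power (0.887 against 0.809), and it offsets the fact that 110 falls short of 117 if 93 is taken as the true requirement.
- **That 44 places are already affected.** Results gives 211 recruited and 167 completed by April 2025. The difference of 44 includes people still in the 6-month follow-up, and no withdrawal or replacement count is reported.

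It can also be said that the word *rerandomized* implies chance still operates, and that assistants know only codes, not contents. Both are fair. Adjusted assignment may keep a random element with a shifted ratio, and blinding limits what a predicted code is worth. Neither point restores the fixed list or its concealment.

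**Conclusion.** The concern holds in this form. The adjustment rule contradicts the fixed blocks, makes late assignments depend on arm-specific losses, and weakens concealment because the staff who generate the sequence also enrol and assign under two codes. The shift is nil with equal losses and reaches 62.5% to one arm at an assumed 25% versus 15% loss. The resulting time-trend bias is small under the drift assumed above (0.02 to 0.03 SD). Predictability is a risk that the article does not allow one to quantify, and it depends on those staff knowing losses by code. If *rerandomized* were meant to touch people already allocated, the problem would be worse, but the text does not say so.

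Separately, 220 with 110 per product cannot describe the intention-to-treat set after any replacement. The 275 rests on 20% loss in every round. None of this shows that the comparison is biased by replacement as such.

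**What to change.** 1. Delete the sentence on re-randomizing and adjusting product numbers. Any additional recruit takes the next number on the unaltered block list, regardless of who withdrew.
2. State that the primary set is everyone ever randomized, in the arm first allocated, including anyone who withdrew and was replaced, and that unequal arms are accepted. Say that 220 is a recruitment target and not the size of that set.
3. Before unblinding, report how many replacements and how many adjusted assignments have been made, if any.

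The cost is a change of wording and a short count. Arms may end slightly unequal, at a power cost of about 0.001 for 92 versus 84. Recruiting beyond 220 need not be forbidden: from an unaltered list it is harmless.

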### Monitoring

Participants are instructed to maintain their regular lifestyle throughout the study duration. We recommend that they adhere to their usual routine regarding the number of meals and dietary plan. If there is a need to use any medication, they are required to inform the PI to ensure proper documentation in the CRF.

To ensure compliance, participants are requested to submit the provided supplement bottles during their visits at 3 and 6 months. The percentage of the leftover supplements in the returned bottles are used to track compliance. The purpose of these data is to evaluate intervention adherence. To account for adherence-related differences in the treatment effect, the compliance percentage is incorporated as a covariate in the statistical analyses. Additionally, subgroup analyses based on adherence levels (high, medium, and low compliance) will be carried out.

Additionally, plasma vitamin E levels are measured at 0, 3, and 6 months to assess the participants’ response to supplementation. In the event of suspected side effects or adverse reactions, participants should promptly report to the PI and seek immediate medical assistance. The PI must assess whether the observed effects are related to the trial and determine if the participant should be excluded from the study accordingly.

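### Compliance, measured after randomization, is a covariate in the analyses with no limit to secondary ones; this conflicts with the intention-to-treat primary analysis and can bias it

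*Protocol article*

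**What the plan says.** Under Methods, Analyses, the primary analysis is intention-to-treat. The section states that "All randomized participants are included in the primary analysis" and that this approach "analyzes participants based on their initial group allocation regardless of whether they adhere to the intervention". A per-protocol analysis is listed separately as secondary.

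Under Methods, Monitoring, "participants are requested to submit the provided supplement bottles during their visits at 3 and 6 months", and the share of softgels left over gives a compliance percentage. The section continues: "To account for adherence-related differences in the treatment effect", "the compliance percentage is incorporated as a covariate in the statistical analyses". It then adds that "subgroup analyses based on adherence levels (high, medium, and low compliance) will be carried out".

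The Discussion says that noncompliance arose mainly because participants had trouble remembering the supplement, and that noncompliant participants' data are kept in the analysis. Its limitations paragraph names cognitive impairment, mobility problems and comorbidities as threats to adherence.

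**The concern.** Compliance is observed only after allocation. Putting it in the model changes the question from the effect of being allocated to TRF to the difference between arms among people with the same compliance. Randomization protects the first comparison but not the second. If the product changes how much people take, and the people who take less also differ in health or memory, holding compliance fixed compares unlike people across arms.

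The covariate also does not serve its stated purpose. A main-effect term assumes one treatment effect at every compliance level. Differences in the effect by adherence would need an interaction, and that would still not be a randomized comparison. The high, medium and low subgroups have the same weakness, since participants select themselves into them.

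At stake are what the primary estimates mean and, under the conditions worked out below, their Type I error. There is also a practical risk: if the text leaves open whether the primary model carries the covariate, adjusted and unadjusted results could both be presented as the planned analysis.

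**Working it through.** **1. The text.** The plan gives no figure to reproduce, so the first check sets the sections side by side.
- Analyses: all randomized participants, by allocation, whatever their adherence.
- Monitoring: compliance is a covariate in the statistical analyses, with no limit to per-protocol, secondary or sensitivity analyses. The adherence subgroups come in a separate, additional sentence, so the covariate is not merely part of them.
- Discussion: keeping noncompliant participants settles who is analyzed, not what the model conditions on.

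No section confines the covariate to secondary work. The conflict does not depend on any number.

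**2. Size of a possible bias.** Inputs from the document: 110 per arm; significance at .05, taken here as two-sided; planning means 3.11 (SD 0.81) and 2.66 (SD 1.25). The last give a difference of 0.45, a root-mean-square SD of √((0.81² + 1.25²)/2) = 1.053, and a standardized effect of 0.45/1.053 = 0.427.

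Assumed inputs, not in the documents: the within-arm compliance-outcome correlation r (size 0 to 0.3), arising from shared causes, and the arm difference in compliance d (0 to 0.5 SD).

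With no true effect, the size of the bias in outcome SD is approximately |r| × d:

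| r (size) | d | Bias (SD) | Share of 0.427 |
|---|---|---|---|
| any | 0 | 0 | 0% |
| 0 | any | 0 | 0% |
| 0.1 | 0.2 | 0.02 | 5% |
| 0.25 | 0.4 | 0.10 | 23% |
| 0.3 | 0.5 | 0.15 | 35% |

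The direction depends on the signs of both links.

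**3. Type I error at r = -0.25, d = 0.4.**
- The variance inflation from the arm difference is 1 + d²/4 = 1.04.
- The standard error of the adjusted effect is √(2/110) × √(1 - 0.25²) × √1.04 = 0.1348 × 0.968 × 1.020 = 0.133.
- The bias in standard errors is 0.10/0.133 = 0.75.
- Two-sided rejection at .05 is then about 11.6%.

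Two simulations of this scenario (4,000 and 10,000 runs, 110 per arm, no true effect) gave adjusted biases of -0.103 and -0.098 SD. Rejection was 11.2% and 11.3% adjusted, against 4.9% and 5.3% unadjusted. With d = 0, adjusted rejection was 4.7%.

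A differently built simulation assumed mean compliance of about 85%, 5 points lower on TRF, and a latent health factor correlated 0.3 with the outcome. It gave a bias of 0.09 SD and 9.5% rejection. With that correlation set to 0, rejection was 4.6%.

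**4. Missing covariate values.** At the 20% dropout in the Sample Size section, 0.20 × 110 = 22 per arm. This is an upper bound on those with no returned bottle. People who leave after month 3 can have a 3-month value. Those without any value drop out of a complete-case model that contains compliance.

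**The case against.** The covariate sentence sits under Monitoring, beside a statement that these data are for evaluating adherence, while the Analyses section describes the mixed-design ANOVA without naming compliance. It could be read as a supplementary adherence analysis, and an analysis plan not shown might say so. However, the sentence carries no such limit, and the subgroups are introduced separately. A reader following this text would put compliance in every model. The intention-to-treat definition does govern who is analyzed and in which arm, and nobody is moved between arms. The conflict is that conditioning on adherence undoes the promise to disregard it.

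Three stronger readings are tempting, and the documents do not support them.
- **That the primary estimates will be biased and the Type I error will not be .05.** This needs both an arm difference in compliance and causes shared with the outcome. For the second, the Discussion offers candidates: memory difficulty, cognitive impairment and comorbidity. For the first, it offers no evidence. The softgels are matched and blinded, and forgetting does not by itself differ by arm.
- **That 0.10 SD or 11% estimates the risk in this trial.** These figures illustrate assumed inputs. The range includes zero.
- **That the intention-to-treat analysis becomes a completer analysis.** Later leavers can have a compliance value. The Analyses section also plans mixed models, with multiple imputation and pattern-mixture models as sensitivity analyses. Those who leave before month 3 contribute no post-baseline outcome in any case. What stands is that no rule covers a missing compliance value, and a complete-case covariate model would not contain all randomized participants.

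**Conclusion.** The point holds. As written, the protocol puts a post-randomization variable into analyses that include the primary one, against its own intention-to-treat definition. That the estimand changes follows from the text alone. Bias and Type I error above .05 are possible, not established: 0 to about 0.15 SD over the assumed range, about 0.10 SD with about 11% rejection in the worked case, and none if compliance does not differ between arms or shares no cause with the outcome. Loss of participants through a missing covariate is bounded at about 22 per arm at 20% dropout and would be smaller if some leave after month 3. It should be corrected, because it reaches the primary analysis.

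**What to change.** In Monitoring and Analyses:
- State that the primary intention-to-treat models do not contain compliance and adjust only for baseline variables.
- Report compliance by arm descriptively.
- Confine compliance-adjusted models and the high, medium and low adherence analyses to supplementary analyses, labelled as non-randomized comparisons.
- If an effect under adherence is wanted, a complier-average effect with randomized arm as instrument is an option beside the per-protocol analysis.

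The cost is wording only, with no new data or visits. Settle it before the product codes are revealed, so that the choice between adjusted and unadjusted results is made blind.

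### The planned adherence subgroups are defined by compliance measured after randomization, so TRF-versus-placebo comparisons within a level could give a misleading supportive claim

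*Protocol article*

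**What the plan says.** Under Monitoring, participants bring back their bottles at the 3- and 6-month visits, and the share of softgels left over measures compliance. Two uses follow. First, "the compliance percentage is incorporated as a covariate in the statistical analyses". Second, "subgroup analyses based on adherence levels (high, medium, and low compliance) will be carried out". The section says that the covariate is meant to capture differences in the treatment effect that relate to adherence. It gives no cut-points for the three levels. It also does not say whether treatment is compared within each level or through an interaction term.

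Under Analyses, the reason for adjusting is given as follows: "To account for the risk of a Type I error as a result of many primary and secondary outcomes, multiplicity correction procedures will be used". The method is that "the Benjamini-Hochberg approach for false discovery rate control will be used in each outcome domain", and results are judged "with statistical significance defined as *P*<.05". Subgroups are not mentioned in that family.

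The same section ranks two analyses: "All randomized participants are included in the primary analysis using the intention-to-treat approach", and "Only participants who complete the study without significant protocol deviations are included in a secondary per-protocol analysis". The adherence subgroups have no stated place in this order.

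**The concern.** Compliance level is an outcome of the treatment period. If the assigned product influences how much people take, or who remains to return a bottle, then TRF and placebo participants at the same level are different kinds of people. The contrast between them then mixes the treatment effect with that difference. Neither an interaction test nor a multiplicity correction removes this, because the grouping variable itself is affected.

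The practical risk is foreseeable. The Discussion reports that non-compliance already occurs. After a non-significant overall result, a significant high-compliance level would invite the statement that TRF works when it is taken. That statement would rest on a comparison that randomization may not protect. It would also come from a set of extra comparisons that the stated false-discovery step does not name.

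**Working it through.** **1. Order of events.** Randomization comes first, then supplementation, then bottle return at 3 and 6 months, and only then the compliance level. A participant who leaves without returning a bottle has no count for that period.

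**2. What a within-level comparison estimates.** Let Y0 be a participant's outcome without TRF, and let L be a compliance level. Then

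mean(TRF, level L) − mean(placebo, level L) = effect of TRF in those TRF participants + [mean Y0 of those who reach L when given TRF − mean Y0 of those who reach L when given placebo].

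The bracket is zero if assignment does not change who reaches or stays in L; otherwise nothing guarantees it. Two places in the article leave room for such a change. Recruitment lets the principal investigator withdraw people for abnormal laboratory values or for not following procedures. Monitoring lets the principal investigator consider exclusion after a suspected reaction. The article gives no compliance or withdrawal figures by arm, so the bracket cannot be sized.

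**3. Multiplicity, conditional on how the levels are tested.** The plan states no error rate for these subgroups, so there is no figure to reproduce.

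Inputs from the article: three levels (Monitoring) and a .05 threshold (Analyses).

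Assumptions: a two-sided test of TRF against placebo in each level, uncorrected; no effect anywhere; independent level statistics z1, z2, z3; an overall statistic z = Σ √wᵢ·zᵢ, where wᵢ is the share of participants in level i; and the overall test at an unadjusted .05. The shares are not given, so a range is shown.

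Any level significant: 1 − 0.95³ = 1 − 0.857375 = 0.143.

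Significant level together with a non-significant overall test (simulation, 6 million draws):

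| Shares (high/medium/low) | Any level, either direction | Any level, favouring TRF | High level, favouring TRF |
|---|---|---|---|
| equal thirds | 11.1% | 5.7% | 1.9% |
| 60/30/10 | 11.0% | 5.7% | 1.5% |

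With a more extreme split of 90/7/3, the first two columns fall to 10.3% and 5.3%.

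For scale, one two-sided test at .05 favours TRF by chance 2.5% of the time. The any-level figure of 5.7% is 5.7/2.5 = 2.3 times that. The figure for the high level alone is below 2.5%, because it also requires the overall test to be non-significant.

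**4. What a correction would do.** At .05/3 per level, the chance of any significant level is 1 − (1 − 0.05/3)³ = 4.9%, and jointly with a non-significant overall test it is 3.1-3.3%. That settles the count of tests and leaves the bracket in step 2 as it was.

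**The case against.** The strongest defence has four parts.

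- **The form of the test is not stated.** The wording would fit an interaction test as well as three separate tests. Test form, cut-points and subgroup multiplicity are commonly left to an analysis plan, which is not shown here. This stands. The percentages are therefore conditional, and missing detail is not the point. What the article does fix is the grouping variable, and step 2 applies to either form of test.
- **Nothing is replaced.** A reader might infer that a null primary result could be overturned by a positive subgroup. The article does not support that. Intention-to-treat on all randomized participants is primary, and no decision rule or efficacy claim is attached to the adherence levels. The false-discovery scheme is also described as suited to exploratory research.
- **The 11% is not the chance of a false claim of benefit.** A reader might take it that way, but it counts all three levels and both directions. For the claim that matters most, high compliance favouring TRF, the figure is 1.5-1.9%. Multiplying across the six primary domains would not help either. Six domains alone, each held at 5% and independent, give 1 − 0.95⁶ = 0.26 with no subgroups at all.
- **Adherence may not differ by arm.** The softgels look alike, participants are blinded, and the Discussion attributes non-compliance mainly to forgetting. If assignment truly has no influence on adherence or retention, the within-level comparison is fair. This is a real mitigation, and it is why the point is worded conditionally. It remains an assumption: similar compliance in the two arms would be reassuring, but would not show that the same kinds of people are in each level.

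**Conclusion.** The concern holds as a flaw in a stated supportive analysis. The plan commits to analyses by a variable measured after randomization, and comparisons within its levels lose the protection of randomization if assignment affects adherence or retention. The size of that bias cannot be derived from the article.

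The multiplicity part is secondary and modest. It rests on uncorrected, two-sided, independent tests within levels, with no true effect and an unadjusted overall test. On those terms an endpoint would show a significant level beside a non-significant overall result about 11% of the time in either direction, about 5.7% in favour of TRF, and about 1.5-1.9% for the high level in favour of TRF. The rates would be lower if the false-discovery step were also applied within levels.

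The primary intention-to-treat comparison is not invalidated by these subgroups. The change is worth making before the blind is broken, because afterwards a choice of adherence analysis could look driven by the results.

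**What to change.** Replace the analyses by compliance level with one complier-average effect per endpoint. Use assigned arm as the instrument and the compliance percentage already recorded as the measure of intake. Define compliance, and the handling of participants without a bottle count, before unblinding. State the exclusion restriction: assignment affects the endpoint only through the TRF taken. The comparison stays a randomized one. Its null test is essentially the intention-to-treat test, so it adds little or no further opportunity for a false positive.

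If results by high, medium and low compliance are still wanted, report them descriptively by arm without P values. Label them exploratory, and state that they cannot support an efficacy claim.

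The cost is some analysis work and wording, with no new data. The downsides are reliance on the exclusion restriction, and no formal test for each compliance level.
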